#### Anthropometric assessment

Anthropometry of both children and their mothers will be assessed in the hospital and the community following protocols proposed by the Food and Nutrition Technical Assistance III Project.^32^ Unclothed or lightly dressed children will be weighed to the nearest 20 g (SECA 383, Hamburg, Germany). Children’s recumbent length (SECA 417, Hamburg, Germany), left mid-upper am circumference (MUAC; Shorr Child MUAC Tape, Weigh and Measure, Olney, Maryland, USA) and head circumference (ShorrTape 65 cm Measuring Tape, Weigh and Measure) will be measured to the nearest 0.1 cm. All measurements will be collected in duplicate and the average of the two measurements will be calculated. If measurements differ by >0.1 kg (weight), or >0.5 cm (length, MUAC, head circumference), the measurement will be repeated a third time and the average of the two closest measurements will be calculated. Maternal weight (SECA 874, Hamburg, Germany), height (SECA 213, Hamburg, Germany) and left MUAC (ShorrTape 65 cm Measuring Tape) will be assessed using a similar approach. Regular standardisation sessions will be implemented to compare the performance of anthropometry teams among themselves and with their supervisors.^33 34^

#### Risk factor and predictor assessment

A broad range of information will be collected using structured questionnaires (online supplementary table 1). Data collection forms were developed in English, programmed in Survey CTO (Dobility, Cambridge, Massachusetts, USA) and translated into Lao for electronic data collection.

Specific questionnaires were developed to assess the child’s birth history, and the child and mother’s health history. Since traditional restrictive postpartum diets are very common in the study population, an extensive questionnaire was developed to record dietary patterns both during pregnancy and the postpartum period. Other questionnaires, such as the assessment of socio-economic status, and child and mother dietary practice questionnaires, were adapted from the Lao Zinc Study.^35^ Since women and children may change their dietary intake due to their presence at the hospital in Luang Prabang, we will ask the mother to report food intake for the days prior to their arrival at the hospital. Household food security will be assessed using the Household Food Insecurity Access Scale,^36^ and social desirability of respondents will be assessed as proposed by Crowne and Marlowe and Menon *et al*.^37 38^ Two brief questionnaires will be used to record the reason for exiting the study by children and mothers, respectively (ie, completion of data collection, withdrawal of consent, death or other reasons).

#### Patient and public involvement

Patients and the public were not involved in the design of this study.

### Case report review

To develop a clinician-guided diagnostic impression of TRD, three expert paediatricians specialised in tropical medicine will review the case reports of each hospitalised child to judge whether a child had TRD using a three-point scale (probable TRD (including classic beriberi); possible TRD and not likely TRD). Specifically, each case report will be reviewed by three expert paediatricians. When there is disagreement (defined as separate raters classifying the same case as probable TRD and not likely TRD) or when there is no agreement (ie, each rater classifies a case into a different category), efforts will be made to reach consensus between the three experts. A case report template was developed for this purpose, which includes the basic demographics of the child (sex, age), the primary concerns of the parents for taking their child to the hospital, relevant data collected during the baseline and follow-up physical examinations (4, 8, 12, 24, 36, 48, 72 hours and hospital discharge), the recovery status over the course of the hospital stay, administered treatments, findings from the echocardiogram and the cranial ultrasound, primary and secondary diagnosis by the LFHC treating physicians at the child’s discharge from hospital, dietary practices and maternal characteristics. The latter include exclusive breast feeding, maternal dietary practices with regard to a restricted postpartum diet and whether the mother experiences tingling in her fingers, an indication that the mother herself may experience clinical manifestations of severe thiamine deficiency. In addition to the case report, the expert panel will be able to review additional study data as needed.

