**Methods and analysis:**

This prospective study will enrol 662 children (aged 21 days to <18 months) seeking treatment for TDD symptoms. Children will be treated with intravenous or intramuscular thiamine (100 mg daily for a minimum of 3 days) alongside other interventions deemed appropriate. Baseline assessments, prior to thiamine administration, include a physical examination, echocardiogram and venous blood draw for the determination of thiamine biomarkers. Follow-up assessments include physical examinations (after 4, 8, 12, 24, 36, 48 and 72 hours), echocardiogram (after 24 and 48 hours) and one cranial ultrasound. During the hospital stay, maternal blood and breast-milk samples and diet, health, anthropometric and socio-demographic information will be collected for mother–child pairs. Using these data, a panel of expert paediatricians will determine TRD status for use as the dependent variable in logistic regression models. Models identifying predictors of TRD will be developed and validated for various scenarios. Clinical prediction model performance will be quantified by empirical area under the receiver operating characteristic curve, using resampling cross validation. A frequency-matched community-based cohort of mother–child pairs (n=265) will serve as comparison group for evaluation of potential risk factors for TRD.

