**Trial registration number:**

NCT03626337.

Strengths and limitations of this studyA standardised case definition for thiamine responsive disorder (TRD) will be proposed, through understanding of the interplay between clinical presentation, response to therapeutic thiamine administration and biochemical analyses, which will help more accurately diagnose TRD among infants and young children.The broad spectrum of eligibility criteria will ensure inclusion of hospitalised infants and young children who may have milder, underlying thiamine deficiency and may respond clinically and benefit from thiamine administration, as well as those with suspected beriberi.Associations between TRD and biomarkers of thiamine status will help establish deficiency cut-off thresholds for thiamine diphosphate and erythrocyte transketolase activity coefficient that are relevant to a population with thiamine deficiency.Due to ethical considerations, this study does not include a placebo control group and will rely on a community comparison group to cross-check risk factors identified in the hospitalised cohort to a healthier population.In addition to the thiamine administration, hospitalised children will continue to receive routine care, such as antibiotics and other medications for concurrent illnesses that may affect the children’s recovery, making the clear distinction between TRD cases and non-responders more challenging.

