## Objectives of study

The primary objective of this study is the development of a case definition for TRD among infants and young children with symptoms consistent with TDD, with the case definition based on those clinical symptoms and other predictors that we find are better able to distinguish those who respond positively to thiamine administration from those who do not respond. As diagnostic tools available to treating physicians may differ by setting, we will repeat analyses after excluding from the set of candidate predictors those that are derived from assessments only available in higher-resource settings, such as laboratory biomarkers and ultrasonography.

A secondary objective is to fill the knowledge gap surrounding biomarkers of thiamine status in at-risk populations. Biomarker cut-offs for TRD will be developed in the hospital cohort and distributions will be characterised in both the hospital and community cohorts. The performance of our proposed cut-off will be compared with the performance of existing literature cut-offs.

Additionally, all identified predictors and biomarker cut-offs will be compared across the community cohort, non-TRD hospital cohort and TRD hospital cohort to assess the prevalence of risk factors among apparently healthy infants and young children and assess the usefulness of the TRD case definition in various settings.

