#### Statistical analysis

Prior to performing statistical analyses, detailed statistical analysis plans will be developed and published online.^39^

Our primary model development objective will seek to achieve case definition models that provide high discrimination capacity and acceptable calibration in external samples, using principled approaches to guard against overfitting biases. It is likely that there will be ambiguity in TRD determination due to a range of potential thresholds for what is considered ‘recovery‘. Consequently, sensitivity analyses may be repeated with different variations of TRD definitions. These definitions will be defined prior to analysis by expert paediatricians. We will follow a three-staged approach to identifying candidate risk factors and selecting among them. In the first stage, investigators will specify risk predictors that could be reliably and validly measured early in the hospitalisation in limited-resource settings and which are plausibly associated with TRD status. In the second stage, we will develop and validate logistic regression models, using TRD status as the dependent variable and using elastic net regression and related approaches to principled variable selection. In the third stage, we will repeat the analysis incorporating more sophisticated diagnostic assessments, such as biomarkers and ultrasound, which are available in higher resource settings. Finally, after each clinical prediction model is developed, we will use resampling methods with 10-fold cross validation to estimate model performance in terms of discriminative capacity, as measured by empirical AUROC, internally and externally.

Our secondary objective of establishing biomarker cut-offs for TRD will follow a similar receiver operating characteristic curve-based approach, except with specific biomarker concentrations as the principle predictor. A weighted evaluation of each cut-offs sensitivity and specificity will be used in a 10-fold cross-validation framework to select the optimal cut-off.^40^

The comparison of predictors, biomarkers and risk factors across the community cohort, non-TRD hospital cohort and TRD hospital cohort will be contextual and dependent on the type of variable considered. Analyses will be primarily descriptive, focused on substantive differences between cohorts, accompanied by visualisations and distribution-appropriate statistical testing.

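### The panel assigning TRD may open any study data, with thiamine biomarkers not excluded, so the label used to set the ThDP and ETKac cut-offs can come to depend on those biomarkers

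*Protocol article*

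**What the plan says.** **The label.** The Case report review section has three paediatricians rate each child as probable, possible or not likely TRD and seek consensus on conflicting ratings. The template is itemised: examinations, recovery status, treatments, "findings from the echocardiogram and the cranial ultrasound", discharge diagnoses, diet and maternal characteristics. No blood biomarker is listed. The section then closes by saying that "the expert panel will be able to review additional study data as needed".

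**The abstract.** It lists a "venous blood draw for the determination of thiamine biomarkers" among the baseline assessments, mentions maternal blood and breast milk, and continues: "Using these data, a panel of expert paediatricians will determine TRD status for use as the dependent variable in logistic regression models".

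**Use of the label.** Under Objectives of study, "Biomarker cut-offs for TRD will be developed in the hospital cohort", and their performance is to be compared with published cut-offs. The Statistical analysis section says that "establishing biomarker cut-offs for TRD will follow a similar receiver operating characteristic curve-based approach, except with specific biomarker concentrations as the principle predictor". The strengths and limitations list names the two markers: "Associations between TRD and biomarkers of thiamine status will help establish deficiency cut-off thresholds for thiamine diphosphate and erythrocyte transketolase activity coefficient". Stage 3 of the model building repeats the TRD regression with biomarkers and ultrasound added as candidate predictors.

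**The concern.** A reference standard used to judge a test should be set without knowledge of that test. Here the access rule is open-ended and the markers under evaluation are part of the study data. If a rater consults ThDP or ETKac to settle a child's status, the marker is then partly predicting itself (incorporation bias).

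Three results are exposed: the new cut-offs, their comparison with literature cut-offs, and the discrimination credited to biomarkers in stage 3. The chosen cut-off would be pulled towards whatever value influenced the ratings.

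Cross-validation offers no protection. It guards against fitting noise in a given label, but here every fold carries the same label. Nor can the problem be undone once ratings have been made with the results in view.

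**Working it through.** **1. Is there a restriction anywhere?** The sections on case review, blood biomarker analysis, breast milk, data management and statistics contain no rule keeping thiamine results from the panel. On timing, ThDP is to be assayed later from blood stored at −80°C, ETK at a laboratory in the UK, and breast milk at a laboratory in the USA. None of these is ordered relative to the panel's work. The access sentence therefore stands unqualified, and the abstract is consistent with it.

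**2. Which analyses share the marker and the label?** The secondary cut-off analysis does, since it runs "with specific biomarker concentrations as the principle predictor", and so does stage 3. The limited-resource models of stages 1-2 do not use biomarkers as predictors.

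**3. Sample size.** It is not at issue. The stated figure reproduces: 662 / (1.88 × 1.25 × 1.25) = 225.4, given as 225.

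**4. How large could the effect be?** The article gives no figure, so this is an illustration on assumed inputs.

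- TRD prevalence p: 11% or 20%. The community-comparison sample size uses groups of 60-106 and 424-470. Taking the smaller group as TRD, 60/530 = 11% and 106/530 = 20%.
- True biomarker AUROC A = 0.60 (assumed).
- A random share f of labels is replaced by the rule that the most deficient share q of children is TRD. Either q = 25% or q = p (assumed).

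Let U be a child's fractional rank on deficiency (1 = most deficient). Then AUROC = (mean U in TRD − p/2) / (1 − p), so the mean U in TRD is p/2 + (1 − p)A. Within the most deficient share q, the mean U is 1 − q/2. After replacement:

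- prevalence p′ = (1 − f)p + fq
- mean U′ = [(1 − f)p(p/2 + (1 − p)A) + fq(1 − q/2)] / p′
- apparent AUROC = (U′ − p′/2) / (1 − p′)

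When q = p this reduces to A + f(1 − A).

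Example with p = 0.11, q = 0.25, f = 0.10:

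- original mean U = 0.055 + 0.89 × 0.60 = 0.589
- p′ = 0.099 + 0.025 = 0.124
- U′ = (0.099 × 0.589 + 0.025 × 0.875) / 0.124 = 0.6467
- apparent AUROC = (0.6467 − 0.062) / 0.876 = 0.667

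| Share f of labels set by biomarker | q = p (either prevalence) | q = 25%, p = 20% | q = 25%, p = 11% |
|---|---|---|---|
| 1% | 0.604 | 0.605 | 0.607 |
| 2% | 0.608 | 0.609 | 0.615 |
| 5% | 0.620 | 0.623 | 0.635 |
| 10% | 0.640 | 0.646 | 0.667 |
| 20% | 0.680 | 0.690 | 0.723 |

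A simulation of 400,000 children with a binormal marker agrees to within 0.002 where it was run (q = 25%; f = 5%, 10% and 20%).

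To put f in children: with both planned 20% allowances, 662 × 0.80 × 0.80 ≈ 424 have follow-up and blood. So 5% is about 21 children and 10% about 42.

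The cut-off shift is not computed, because the article does not give the weights on sensitivity and specificity. Its direction is towards the value the raters used.

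**The case against.** The strongest reply is that the design as described keeps biomarkers out of the rating. The template goes down to whether the mother has tingling fingers, yet names no blood biomarker. The Study design section defines cases by their response to thiamine. The assays are done later or off site, so results may not exist when the panel meets. The Introduction says there are no agreed cut-offs for ThDP or ETKac, which makes them awkward to rate from. Access rules could also sit in a full protocol or panel manual that is not shown.

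Most of this stands as mitigation. A reader might infer that raters will consult biomarkers for ambiguous children, or that the secondary objective is already circular. The documents support neither. They say what the panel may do, and disagreement is handled by discussion without mention of biomarkers. The abstract's wording is a summary and does not prove that biomarkers reach the panel.

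The illustration also has limits. The share f has no basis in the article. The fixed quartile rule labels more children TRD than the assumed prevalence. Labels are replaced at random and decided entirely by the marker, whereas real use would fall on unclear cases and be weighed with clinical findings.

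The reply does not remove the point. The article is not silent: it states an access rule for its reference standard, and that rule overrides the protection of the template. Protection by late assays would be accidental, because no order is fixed. The possible sensitivity analyses with other TRD definitions would be a partial check only if one rested on recovery alone, which the article does not say.

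**Conclusion.** The point holds as a permitted risk, not a demonstrated bias. The access rule allows the TRD label to depend on the markers it is meant to evaluate, and the planned analysis has no step that would detect or correct this.

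Exposure is confined to the secondary cut-off objective and the stage-3 models. A reader might infer that the whole case definition is compromised. It is not, because the limited-resource models share no biomarker with the label and are largely unaffected.

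The size depends wholly on how many labels a biomarker would decide, which is unknown. At 1-2% the effect is negligible. At 20%, a weak marker (true AUROC 0.60) would appear at or near the 0.70 that the sample size section treats as clinically useful. These figures rest on the assumptions in the working and are not a forecast.

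A correction is warranted because it is simple before rating and impossible afterwards.

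**What to change.** Replace the open access sentence with: the panel may review additional clinical study data, except the child's and mother's thiamine biomarkers and breast-milk thiamine, which stay sealed until all ratings and consensus decisions are locked. Record for each child which extra items were opened.

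The cost is one protocol sentence, an access restriction in the data system and a short log. There is no added burden on patients. The downside is that raters lose biomarker information when settling unclear cases. That loss is small, because TRD is meant to be defined by response to thiamine.

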### Data management and statistics

#### Electronic data collection, data management and data quality control

Participants will be given a unique four-digit numeric study ID code, which will link all data collected from the individual. To link the data from a child–mother pair, the same four-digit ID code will be given to each with the exception that the mothers’ data will be identified with the letter ‘M’ before the four-digit ID code.

All data will be collected electronically using Survey CTO, and pre-designed, pre-coded paper forms will be available for backup, if needed. Data collection forms were developed in a customised Survey CTO application by a UC Davis data manager, and, where appropriate, forms include pre-determined checks and range validations. Forms will be deployed onto Samsung tablets (Samsung Galaxy Tab. 3 V, Seoul, South Korea) equipped for mobile internet access. All data forms collected will first be reviewed by one of two study data managers and then synchronised onto a central server.

Data quality checks will be run weekly and track information such as form completion, internal consistency, specimen sample processing, realistic data ranges, eligibility criteria, child’s timeline within the study and translation of local languages to English. Feedback will be regularly communicated to study staff to ensure consistent high-quality data collection.

#### Sample size

For our primary research question, we aim to develop and compare clinical prediction rules that are useful in determining which children with TDD-like symptoms would respond favourably to thiamine treatment. Given the context of the study, there is uncertainty around the expected prevalence of TRD in our sample and so we anticipate that between 10% and 90% of the hospitalised cohort will be classified as responders. Assuming that a clinically useful discriminative capacity will correspond to an area under the receiver operating characteristic curve (AUROC) of 0.70 for the responders versus non-responders classification, we will test the null hypothesis that the AUROC is 0.5 using a two-sided test with alpha=0.05. To account for the selection of independent variables for our multivariable model, we derived a variance inflation factor of 1.88 by computing the ratio of the χ^2^ non-centrality parameters corresponding to 95% power, two-sided alpha, with 10 and 1 df, respectively (24.386 (for 10 df) divided by 12.995 (for 1 df)). Additional variance inflation factors of 1.25 and 1.25 were needed to account for 20% loss to follow-up and 20% probability of blood collection failure, respectively. Hence, we anticipate that a total enrolment of 662 hospitalised children will, after correcting for these three variance inflation factors, result in an effective sample size of 225 for power and sample size purposes. According to the SAS ROCPOWER macro (SAS V.9.4; SAS Institute), an effective sample size of 225 would provide at least 90% power to detect a model with a discriminative capacity corresponding to an AUROC of 0.70, under two-sided testing with alpha=5% given a TRD prevalence of between 11% and 89%.

For our secondary research questions concerned with describing TRD risk factors across a community comparison cohort and our two hospital cohorts, we plan to enrol 212 region, age and sex frequency-matched children (increased to 265 after adding the inflation factor of 1.25 for potential blood collection failure). Given a hospital cohort split between TRD groups of sizes 60–106 and 424–470, this would provide at least 80% power to detect an independent variable for which a 1 SD increase is associated with an adjusted OR of 1.6, under two-sided testing (of the null hypothesis that the adjusted OR is 1) with alpha=5%, even when other covariates in the models account for as much as 20% of the variation in that independent variable. For a binary risk factor present in 20% of children, the detectable adjusted OR under the stated assumptions would be 2.45. Hence, we anticipate having adequate statistical power to detect risk factors associated with moderate to strong incremental discriminative capacity.

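### The variable-selection inflation factor is taken at 95% power but supports a 90% power claim; matched to 90%, the effective sample size is about 217, not 225

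*Protocol article*

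**What the plan says.** All of this is in the protocol article, Sample size.

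- The primary test: "we will test the null hypothesis that the AUROC is 0.5 using a two-sided test with alpha=0.05", against an alternative of "area under the receiver operating characteristic curve (AUROC) of 0.70 for the responders versus non-responders classification".
- The allowance for variable selection: "we derived a variance inflation factor of 1.88", the ratio of the non-centrality parameters (24.386 and 12.995) "corresponding to 95% power, two-sided alpha, with 10 and 1 df, respectively".
- Two further allowances: "Additional variance inflation factors of 1.25 and 1.25 were needed to account for 20% loss to follow-up and 20% probability of blood collection failure".
- The result: 662 enrolled children reduce to an effective 225, and "an effective sample size of 225 would provide at least 90% power" for prevalences between 11% and 89%.
- The expected prevalence is slightly wider than that: "we anticipate that between 10% and 90% of the hospitalised cohort will be classified as responders".

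The section gives no reason for using 95% power in the factor and 90% in the claim.

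**The concern.** The factor converts a single-df sample size into one that keeps the same power for a 10-df test. It does this only if both non-centrality parameters are taken at the power being claimed. The ratio falls as power rises, so a 95% ratio used for a 90% claim understates the penalty. The understatement falls at the two ends of the prevalence range, because those are the points at which power is only 90%.

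The effective sample size and the prevalence range with 90% power are the stated justification for enrolling 662 children. Both come out slightly too favourable, and the stated range already stops short of the anticipated 10% to 90%.

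**Working it through.** **Inputs (Sample size section).** Two-sided alpha 0.05; AUROC 0.70 against 0.50; 10 and 1 df; factors 1.25 and 1.25 (product 1.5625); 662 enrolled.

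**1. The plan's own figures reproduce.** The non-centrality parameter is the value at which a non-central chi-square exceeds its 5% critical value with the required probability.

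- At 95% power: 24.386 (10 df) and 12.995 (1 df), ratio 1.877, printed as 1.88.
- Effective N = 662/(1.88 × 1.5625) = 225.4, printed as 225.
- A null-variance AUROC formula matches the printed range: power = Φ(0.20/SE₀ − 1.96), with SE₀² = (n + 1)/(12·n₁·n₀). For n = 225 at 11% prevalence, n₁ = 24.75 and n₀ = 200.25, so SE₀ = 0.0616 and power = 90.05%. This formula is symmetric, so 89% gives the same result.

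**2. The ratio at other power levels.**

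| Power | 10 df | 1 df | Ratio | Effective N from 662 |
|---|---|---|---|---|
| 80% | 16.241 | 7.849 | 2.069 | 204.8 |
| 85% | 18.090 | 8.978 | 2.015 | 210.3 |
| 90% | 20.532 | 10.507 | 1.954 | 216.8 |
| 95% | 24.386 | 12.995 | 1.877 | 225.8 |

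At the claimed 90%, effective N = 662/(1.954 × 1.5625) = 216.8, about 217. The drop from 225 is 8/225 = 3.6%. Holding 225 would take 225 × 1.954 × 1.5625 ≈ 687 enrolled.

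**3. A check that needs no AUROC formula.** If the effective sample gives exactly 90% on 1 df (non-centrality 10.507) and 1.88 is used, the 10-df test has non-centrality 10.507 × 1.88 = 19.75. Its power is 88.6%.

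**4. AUROC power at 11% prevalence.**

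| Variance formula | n = 225 | n = 217 |
|---|---|---|
| Null variance | 90.0% | 89.0% |
| Hanley-McNeil | 90.2–90.4% | 89.1–89.4% |
| Obuchowski | 90.7–91.6% | 89.6–90.7% |

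Binormal simulation with 24 cases and 193 non-cases (40,000 runs) gives 91.3% for the Wilcoxon test and 91.6% for DeLong. A logit-scale formula gives 82.8% at n = 225; it does not match the printed claim and was set aside.

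**5. Where the 90% limit falls.** Under the null variance the lower limit moves from 11.0% (n = 225) to 11.4% (n = 217), and the upper limit mirrors it at 88.6%. Under the other formulas the upper end does not bind: at 89% prevalence with n = 217, Hanley-McNeil gives 93.8% to 98.0% and Obuchowski 91.6% to 94.8%.

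**6. Where the mismatch stops mattering.** With n = 225 and the null variance, power reaches about 95% at 14% prevalence (and at 86%). Between those points a 95% factor is not too small.

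**7. The anticipated ends, 10% and 90%.** Power there is below 90% under the null variance, so the 90% factor is itself slightly too small. The ratio is about 2.0 at 86% power. Solving for a factor that matches its own power gives 2.01, effective N = 662/(2.01 × 1.5625) ≈ 211, and power of about 85%.

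**The case against.** The strongest reply is that every printed number reproduces, the 95% level is openly stated, and nothing in the design turns on the difference. That is correct: this is an inconsistency between two stated power levels, not a slip in arithmetic.

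The factor is also a rough device. The Statistical analysis section plans elastic net selection and cross-validated AUROC, so no 10-df test will actually be run, and the two 20% allowances are round planning guesses. This limits how much weight a third significant figure can bear. It does not explain why the factor and the claim use different power levels.

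The 95% choice is defensible over most of the range, since power is 95% or more from about 14% to 86% prevalence. That stands, and it confines the point to roughly three percentage points of prevalence at each end.

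A reader might infer that the claim of 90% power at 11% prevalence is false. The document does not support that. It names the SAS macro but not its variance formula. The symmetric 11% to 89% range is compatible with a null variance, but that is inference, and some Obuchowski variants and the simulation stay above 90% at n = 217. Nor is 12% to 88% established as the corrected range: it is a null-variance result rounded to whole percents, and the other formulas keep 89% prevalence above 90% power.

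**Conclusion.** The point holds as a minor inconsistency. The factor is computed at 95% power and supports a claim at 90%. Matching the two raises it from 1.88 to 1.954 and lowers the effective sample size from 225 to about 217. The direction is anti-conservative where single-df power is close to 90%, and the cost there is about 1 to 1.5 percentage points. At 11% prevalence, power of at least 90% is not assured: it lies at about 89% to 91%, depending on the variance formula.

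The non-centrality ratios and the effective sample size follow from the section's own inputs. The power figures by prevalence rest on assumed variance formulas, because the macro's own is not given.

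**What to change.** In the Sample size section:

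- Compute the variable-selection factor at the power claimed: 20.532/10.507 = 1.954. Alternatively, state why 95% was used.
- Restate the effective sample size as about 217.
- Re-run the ROCPOWER macro with 217 and restate the prevalence range with at least 90% power. Expect about 11.4% to 88.6% if the macro uses a null variance.
- If power at the anticipated 10% and 90% ends is quoted, do not carry 1.954 over. Use a factor that matches the power there, about 2.0, which gives roughly 85% under the null variance.

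The cost is three corrected figures and one macro run, with a slightly less favourable power statement. Enrolment stays at 662.
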